## Abstract

**Background:**

Borderline personality disorder is a severe mental disorder that usually has its onset in youth, but its diagnosis and treatment are often delayed. Psychosocial ‘early intervention’ is effective in improving symptoms and behaviours, but no trial has studied adaptive functioning as a primary outcome, even though this remains the major persistent impairment in this patient group. Also, the degree of complexity of treatment and requirements for implementation in mainstream health services are unclear.

The primary aim of this trial is to evaluate the effectiveness of three forms of early intervention for borderline personality disorder in terms of adaptive functioning. Each treatment is defined by combining either a specialised or a general service delivery model with either an individual psychotherapy or a control psychotherapy condition.

**Methods/design:**

The study is a parallel-group, single-blind, randomised controlled trial, which has randomised permuted blocking, stratified by depression score, sex and age. The treatments are: (1) the specialised Helping Young People Early service model plus up to 16 sessions of individual cognitive analytic therapy; (2) the Helping Young People Early service plus up to 16 sessions of a control psychotherapy condition known as ‘befriending’; (3) a general youth mental health care model plus up to 16 sessions of befriending. Participants will comprise 135 help-seeking youth aged 15–25 years with borderline personality disorder. After baseline assessment, staff blind to the study design and treatment group allocation will conduct assessments at 3, 6, 12 and 18 months. At the 12-month primary endpoint, the primary outcome is adaptive functioning (measures of social adjustment and interpersonal problems); secondary outcomes include measures of client satisfaction, borderline personality disorder features, depression and substance use.

**Discussion:**

The results of this trial will help to clarify the comparative effectiveness of a specialised early intervention service model over and above general youth mental health care, along with the contribution of individual cognitive analytic therapy over and above specialised general clinical care in early intervention for borderline personality disorder. Consequently, the findings will also inform the level of training and competency required for effective delivery of early intervention services.

**Trial registration:**

Registered with the Australian New Zealand Clinical Trial Registry ACTRN12610000100099 on 1 February 2010.

## Background

Borderline personality disorder is a severe mental disorder that is characterised by a pervasive pattern of impulsivity and instability in emotion regulation, interpersonal relationships and self-image [1]. Borderline personality disorder affects up to 3 % of the population [2, 3] and is common in psychiatric practice, affecting around one in five outpatients [4]. It is associated with high levels of health resource usage [5] and with adverse long-term outcomes that include severe and persistent functional disability [6], high family and carer burden [7], physical ill health [8, 9] and premature mortality [10], including a suicide rate of 8 % [11].

Although borderline personality disorder usually has its onset in the period between puberty and emerging adulthood (young people), diagnosis is often delayed and specific treatment for the disorder is rarely offered at this early stage [12, 13]. When treatment is eventually offered, functional impairment and iatrogenic complications are already entrenched, limiting the effectiveness of treatment, especially upon functional outcomes [6, 14].

The past two decades has seen evidence establishing that personality disorder diagnoses can be made prior to age 18 years [15] and that there is no point of rarity with personality disorder in adults [12]. Moreover, numerous reviews (for example, [16–19]) have concluded that borderline personality disorder is a unitary construct across the life course in terms of phenomenology, structure, stability, validity and morbidity. This knowledge has sanctioned the diagnosis of personality disorder in young people [20, 21] and has led to the first wave of randomised controlled trials (RCTs) of psychosocial treatments for borderline personality disorder in adolescents, which are summarised elsewhere [12, 22]. These treatments include cognitive analytic therapy (CAT) [23] delivered within the Helping Young People Early (HYPE) program [24], Emotion Regulation Training (ERT) [25, 26], Mentalisation-Based Treatment for Adolescents (MBT-A) [27], and Dialectical Behaviour Therapy for Adolescents (DBT-A) [28].

Overall, these trials have emphasised the importance of diagnosing and treating borderline personality disorder in young people, and the key findings support the effectiveness of psychosocial treatments for adolescents with either the features of, or full-syndrome, borderline personality disorder. All treatments, including good clinical care (GCC), treatment as usual (TAU) and enhanced usual care (EUC), were associated with improvement on outcome measures that included internalising and externalising psychopathology, depressive symptoms, borderline personality disorder features, quality of life, deliberate self-harm, and suicidal ideation. However, the structured interventions (CAT, GCC, MBT-A, DBT-A) generally outperformed TAU or EUC, except in the case of ERT.

These findings largely mirror those in adults with borderline personality disorder, where various specialist treatments seem to have similar effects despite distinct theories and interventions [14]. It remains unclear what role specific components of treatment (service model versus individual psychotherapy) might play in outcome in these trials. Such findings raise the challenging idea that specialised individual psychotherapy might not be the *sine qua non* of treatment for borderline personality disorder [12]. These psychotherapies are especially resource-intensive in terms of training, supervision and implementation, and this has important implications for the cost effectiveness of treatments. It is unclear what level of treatment complexity is required for effective intervention and, therefore, how treatments might be implemented in mainstream health services to address the high prevalence of borderline personality disorder. Therefore, it is important to control for some of the ‘common factors’ of psychotherapy, such as time in therapy, participant expectations and positive experiences of therapy.

These trials have used a range of comparison treatments, including manualised GCC [29], non-manualised TAU [25–27], and non-manualised EUC [28]. The absence of manuals or checks for treatment adherence or competency for TAU and EUC represent significant limitations to these studies. There was likely to be wide variation in practices among these treatments, and it cannot be assumed that TAU or EUC are equivalent or have similar effects. Moreover, TAU might include poor practice [29] or act as a *nocebo*, whereby potentially harmful effects arise from a placebo [22], which might inflate the effect size for the active treatment. Also, of the treatments studied, CAT, GCC, MBT-A and DBT-A are systematised interventions with individual and family components that were delivered within a comprehensive mental health service. However, this service model was manualised only for CAT and GCC.

A key point of difference among the studies is that the HYPE/CAT and ERT studies were primarily focused upon early intervention for borderline personality disorder, whereas the MBT-A and DBT-A studies were primarily focused upon suicidal and self-harming behaviour. It is unclear whether the patient samples in these studies are comparable. Not all treatment with young people is “early intervention” [12], and it is possible that participants were enrolled at different phases of illness (first-presentation patients through to those with enduring disorder). Also, the above RCTs combined ‘subthreshold’ individuals with features of borderline personality disorder who did not meet the full DSM-5 diagnosis (<5 diagnostic criteria) and those with the full-syndrome disorder (5–9 diagnostic criteria). This combines ‘indicated’ prevention with early intervention [13], and it is unclear whether treatment effects might differ among the two forms of intervention. Moreover, these RCTs restricted their inclusion criteria to adolescents (aged 12 to 19 years). Given the continuity of borderline personality disorder across adolescence and emerging adulthood [13], early intervention trials need to include new onset cases across the typical age of onset for the disorder.

Another key limitation is that the primary outcome measures for all these RCTs generally focus on symptoms and behaviours. It has become evident among young people and adults that these features of borderline personality disorder naturally attenuate over time but that impairments in adaptive functioning (vocational functioning and interpersonal relationships) remain stably poor, have proven to be refractory to treatment and should be a primary focus of treatment [12, 14].

### Aims and hypotheses

The overall purpose of this study is to evaluate the effectiveness of three forms of early intervention for adolescents and emerging adults (youth) with borderline personality disorder. The three early interventions vary in their degree of complexity, as determined by different components of service delivery (HYPE versus a general youth mental health service (YMHS)) and individual psychotherapy (CAT versus befriending (BEF)). The three early interventions are (in order of increasing complexity): YMHS + BEF, HYPE + BEF, and HYPE + CAT. The findings of this trial will help to clarify the level and complexity of services and treatments required for effective early intervention for borderline personality disorder.

The specific study aims are to: (i) elucidate whether a specialist early intervention service (HYPE) in addition to CAT (HYPE + CAT) will lead to superior outcomes as compared with the HYPE + BEF and the YMHS + BEF interventions; and (ii) determine whether there is a difference in effectiveness between the HYPE and YMHS service models.

The primary hypothesis is that at the 12-month primary endpoint participants receiving HYPE + CAT will have better outcomes on the primary (social adjustment and interpersonal problems) and secondary (borderline personality disorder symptoms, suicidal ideation, self-injury, depression, alcohol and substance use) outcome measures than those in the HYPE + BEF and YMHS + BEF interventions.

A secondary hypothesis is that at the 12-month primary endpoint, those treated with the HYPE model will have better outcomes on primary and secondary outcome measures than those young people being treated with the YMHS model.

## Methods

### Study design

This study is a parallel group, single-blind RCT comparing three groups: HYPE + CAT, HYPE + BEF, and YMHS + BEF. A full factorial design ( that is, including a fourth treatment arm comprising YMHS + CAT) was not implemented in order to meaningfully differentiate HYPE from YMHS. The HYPE service model incorporates the theory and principles of CAT, without CAT necessarily being used as an individual therapy. This is a key point of differentiation from usual youth mental health service models. If CAT were introduced at the YMHS site it would change usual YMHS practice (that is, the YMHS would represent a specialised rather than generalised service), thus limiting the external validity of this intervention.

The study design was developed in accordance with Good Clinical Practice (GCP) Guidelines and Standard Protocol Items; Recommendations for Interventional Trials (SPIRIT [30]). Figure 1 summarises the trial design. The trial is registered with the Australian New Zealand Clinical Trial Registry (ACTRN12610000100099) and has been approved by the Melbourne Health Human Research Ethics Committee (HREC2010.055).

**Fig. 1 Fig1:**
[figure not shown]
CONSORT flow diagram for Monitoring Outcomes of Borderline personality disorder in Youth (MOBY) trial. Flow diagram of MOBY study design

### Setting

The HYPE + CAT and HYPE + BEF treatments are being delivered at the HYPE Clinic at Orygen Youth Health [24]. Orygen Youth Health is the state-funded specialist mental health service for 15- to 25-year-olds living in western metropolitan Melbourne, Australia. YMHS + BEF is being conducted at *headspace* in western metropolitan Melbourne [31], which is part of a national network of federally funded youth (12-to 25-year-olds) mental health clinics that is managed independently of Orygen Youth Health. It has a similar multidisciplinary outpatient staffing profile and services a similar catchment area to Orygen Youth Health. Therefore, the clientele of the two services are socio-demographically similar. Should the need arise, headspace patients have access to Orygen Youth Health’s after-hours crisis and inpatient services.

### Participants

All participants provide written informed consent. Participants comprise help-seeking young people who either self-refer or are referred to the Orygen Youth Health or headspace intake systems. Broad inclusion criteria are used to maximise the external validity of the trial:Aged 15–25 years, inclusiveAbility to give informed consent and to comply with study proceduresFluency in EnglishA Structured Clinical Interview for DSM-IV Axis II Disorders (SCID-II [32]) diagnosis of borderline personality disorder

Exclusion criteria are:Structured Clinical Interview for DSM-IV Axis I Disorders (SCID-I/P [33]) psychotic disorder within the past 12 monthsLifetime SCID-I/P diagnosis of DSM-IV schizophrenia spectrum disorder, bipolar I or II disorder.Psychiatric condition due to a medical conditionSevere disturbance, such that the person is unable to comply with either the requirements of informed consent or the study protocolPrior evidence-based treatment for borderline personality disorderNot meeting the clinical services’ eligibility criteria (for example, catchment area)

### Enrolment and randomisation

Patients at Orygen Youth Health are routinely screened using the 15 self-report borderline personality disorder items from the SCID-II Personality Questionnaire (SCID-II PQ) [32]. Patients at headspace are optionally screened using the SCID-II PQ. Published data from a previous study at Orygen Youth Health [34] indicate that a cut score of >12 has adequate sensitivity and good specificity and negative predictive value for BPD in youth. All patients scoring >12 are considered for eligibility, along with other trial inclusion criteria. In addition, patients who might screen negative for BPD (SCID-II PQ score ≤12) or who eluded screening but are identified by clinicians as meeting criteria for BPD using the SCID-II borderline personality disorder module [32] are also considered for eligibility, along with other trial inclusion criteria.

Participants are invited to participate by the trial coordinator, who contacts the young person (and their parent or legal guardian for those under 18 years) to introduce the study and to offer an appointment to obtain written consent. After the trial coordinator obtains written consent, a research assistant or the trial coordinator conducts the baseline assessment. All participants receive assertive case management, crisis care and general psychiatric care during the pre-screening and assessment phase. Once eligibility for the trial is confirmed, the trial coordinator randomly and consecutively assigns participants to one of the three interventions in a ratio of 1:1:1 using a password-protected computer program with a randomisation sequence that was computer-generated by an independent statistician. Treatment allocation uses randomised permuted blocking, and participants are stratified by age (cut point of age 18 years), sex and the Centre for Epidemiological Studies Depression Scale Revised (CESD-R) [35] score (cut point = 37, which is the mean score for borderline personality disorder patients on entry to HYPE), thus minimising these potentially confounding factors. Following randomisation to a treatment group, the trial coordinator then randomly assigns participants to the next available trial clinician using a separate randomisation sequence that was also computer-generated by an independent statistician. The trial coordinator contacts the participant and the treating service to inform them of the treatment group and clinician allocation. The clinician then contacts the participant to arrange the first appointment. Thus, the trial coordinator conducts the consent and randomisation procedures separately from the blinded research assistants, using independently derived, password-protected, computer-generated randomisation sequences.

The research assistants conduct all follow-up assessments. The study design and the treatment group assignment are concealed from the research assistants conducting the assessments. Blinding of the research assistants is achieved and maintained by having a specially written version of the trial protocol that removes all references to the three-group design and to any form of treatment. Most research assessments are conducted in the community or at an Orygen Youth Health assessment clinic where no community treatment takes place. Research assistant contact with clinical staff is minimised, and all trial participants, trial clinicians and other staff are regularly reminded of the importance of maintaining the blinding of the research assistants. The research assistants are aware that they are blind to elements of the study. Blinding of the research assistants will be tested at the end of their employment or the end of the study using an online self-report instrument designed specifically for the study. The study’s biostatistician is also blinded with respect to the randomisation.

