### Statistical analyses and sample size determination

To determine whether there are group differences on the primary and secondary outcome measures at 12 months, a series of mixed effects model repeated measures analysis of variances models (MMRM) will be employed. The within groups factor will be time, and the group will serve as the between subjects factor. MMRM is a preferred method for analysing clinical trial data in psychiatry in comparison with the more traditional repeated measures analysis of variance and analysis of covariance models [55]. MMRM is advantageous because it includes all existing data in the model, there is no imputation or substitution of missing data, dispersion and correlation can occur at all time points, and sensitivity analysis can be successfully conducted. Within these models, planned comparisons will be used to determine whether HYPE + CAT is superior to the other two interventions, and whether the HYPE service model leads to better outcomes compared with YMHS.

Power and sample size calculations have been based on a one-way analysis of covariance model with baseline values as the covariate, and the outcome measures as the dependent variables. It is assumed that the baseline covariate will account for 50 % of the variance in an outcome measure. Based on our published data [29, 56], we expect to find medium treatment effects on the primary outcome measures of interpersonal problems and social adjustment. Alpha has been set at 0.05 and power (1-β) for the study at 0.80. Given these parameters, we require 40 participants per group (120 in total) with at least two data points. Based upon the 14 % attrition rate in our previous randomised control trial we intend to recruit at least 45 cases per group.

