## Discussion

The current trial extends previous research and addresses the following questions. What is the comparative effectiveness of three different levels of complexity of early intervention for borderline personality disorder? What is the comparative effectiveness of a specialised early intervention service model over and above general youth mental health care in early intervention for borderline personality disorder? What is the contribution of individual cognitive analytic therapy over and above specialised general clinical care in early intervention for borderline personality disorder? Is early intervention for borderline personality disorder effective for emerging adults as well as for adolescents?

In order to answer the above questions, the trial separately evaluates early intervention, independent of indicated prevention, by only including full-syndrome borderline personality disorder. This has an added advantage of reducing heterogeneity among the sample. The trial also extends the age range of new onset cases studied from 15–18 to 15–25 years. It also focuses upon functional outcomes, reflecting recent findings that this aspect of borderline personality disorder is stably poor over long-term follow-up, refractory to current treatments, and should be the primary focus of treatment outcome studies for borderline personality disorder [6, 12, 14].

While the trial design has attempted to address many problems identified in previous studies, some problems are anticipated. Safety measures for the trial mean that participants who drop out of the trial intervention but who require continuing treatment in a mental health service will be eligible for referral to Orygen Youth Health, meaning that they might receive HYPE + CAT, which is the default treatment offered at Orygen. This will be examined in secondary analyses.

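### The stated model has only time and group although randomisation is stratified by age, sex and CESD-R; followed as written, standard errors are too large and tests conservative wherever the strata predict outcome

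*Protocol article*

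**What the plan says.** Protocol article, Enrolment and randomisation: permuted blocks are used to allocate to "one of the three interventions in a ratio of 1:1:1", and "participants are stratified by age (cut point of age 18 years), sex and the Centre for Epidemiological Studies Depression Scale Revised" score, the last cut at 37. That makes 2 × 2 × 2 = 8 strata. The stated reason is balance: "thus minimising these potentially confounding factors".

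Statistical analyses and sample size determination: the analysis is an MMRM. Its structure is given as "The within groups factor will be time, and the group will serve as the between subjects factor". Within it, "planned comparisons will be used to determine whether HYPE + CAT is superior to the other two interventions", and a second comparison sets the HYPE service model against YMHS. The sample size rests on a "one-way analysis of covariance model with baseline values as the covariate", assuming that "the baseline covariate will account for 50 % of the variance in an outcome measure". The stratification factors appear in neither model.

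Discussion: the last of four questions that the trial is said to address is "Is early intervention for borderline personality disorder effective for emerging adults as well as for adolescents". No aim, hypothesis or planned comparison in the article involves age. The one secondary analysis named there concerns people who leave trial treatment and may then receive HYPE + CAT.

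**The concern.** Stratified blocking makes the arms alike on the three factors, so the treatment estimate varies less from one randomisation to another than it would under simple randomisation. A model that leaves the factors out cannot see this. Their variance stays in the residual, and the standard error is computed as if the balance had arisen by chance. Intervals come out wider than they need be, and the test rejects less often than its nominal level. The planners regarded the factors as possibly related to outcome, so a gain from adjusting for them is plausible by their own account.

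The age question is a smaller matter. Age 18 is a stratum boundary and the Discussion promises an answer by age, but no stated comparison would supply one. All three arms are active interventions, so the trial has no comparator against which to call early intervention effective in either age group. It can show only whether differences between interventions change with age.

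**Working it through.** **Inputs from the article.** 40 evaluable per group (120 in total); baseline explains 50% of outcome variance; alpha 0.05; power 0.80; 1:1:1 permuted blocks; three binary stratification factors.

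**Assumptions, because the article gives no figure.** A medium effect is d = 0.5 between two arms; tests are two-sided; blocks of 6; stratum prevalences of 40%, 80% and 50%; and a share q of the variance left after baseline that the three factors explain, taken from 0% to 30%.

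**The stated sample size.** Take an omnibus three-group ANCOVA with evenly spaced means spanning 0.5 SD:
- f = sqrt(2 × 0.25² / 3) = 0.204.
- Adjusted for baseline, f = 0.204 / sqrt(1 − 0.50) = 0.289.
- Required N = 119, or 40 per group, which reproduces the article.

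Other readings of a medium effect give other numbers (for example f = 0.25 gives N = 81). The stratification factors enter none of them, so the 40 does not depend on this point.

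**Pairwise precision without the factors.** SE = sqrt(2 × 0.5 / 40) = 0.158 SD. The detectable difference at 80% power is 2.8 × 0.158 = 0.44 SD, and power at d = 0.5 is 0.885.

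**Effect of leaving the factors out.** Stratified permuted-block allocation was simulated with N = 120 and 8 strata, and analysed by ANCOVA on baseline (4,000 runs under no effect, 2,000 at d = 0.5). Each cell shows the result without / with the three factors.

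| q | Mean reported SE | Actual SD of estimate | Type I error | Power, d = 0.5 |
|---|---|---|---|---|
| 0% | 0.1584 / 0.1586 | 0.1541 / 0.1545 | 0.0420 / 0.0425 | 0.883 / 0.8825 |
| 10% | 0.1586 / 0.1507 | 0.1491 / 0.1484 | 0.0357 / 0.0438 | 0.886 / 0.9095 |
| 20% | 0.1590 / 0.1421 | 0.1448 / 0.1436 | 0.0302 / 0.0535 | 0.895 / 0.930 |
| 30% | 0.1588 / 0.1329 | 0.1354 / 0.1319 | 0.0240 / 0.0480 | 0.898 / 0.959 |

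The actual spread of the estimate is nearly the same in both analyses. The reported SE is what differs. Simulation error on each type I figure is about sqrt(0.05 × 0.95 / 4000) = 0.003, so the 0.042 at q = 0% is mostly noise, and it is the same in both analyses. As a cross-check, perfect balance gives type I error 2 × (1 − Φ(1.96 / sqrt(1 − q))) = 0.039, 0.028 and 0.019 for q = 10%, 20% and 30%. The simulated values at 20% and 30% sit slightly above because incomplete blocks leave some imbalance.

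**How the factors must enter a repeated-measures model.** The article does not say whether baseline is a level of time. Suppose it is, and the effect is the difference between arms in change from baseline:
- The correlation is sqrt(0.50) = 0.707, and the variance of change is 2 × (1 − 0.707) = 0.586.
- SE = sqrt(2 × 0.586 / 40) = 0.171.
- A factor entered without a time interaction shifts all visits equally and cancels from the change. A two-time-point simulation at q = 20% gave 0.171 with and without it.
- With the factor-by-time term, the variance of change falls to 0.586 − 0.20 × 0.5 = 0.486, and SE = sqrt(2 × 0.486 / 40) = 0.156 (simulated 0.155).

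**Age by arm, 40 per arm.** SE = sqrt(0.5) × sqrt(2/(40p) + 2/(40(1 − p))), where p is the share under 18. The article does not give p.

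| p | SE | Detectable at 80% power (2.8 × SE) | Power for 0.5 SD |
|---|---|---|---|
| 50% | 0.316 | 0.89 SD | 0.35 |
| 30% | 0.345 | 0.97 SD | 0.31 |
| 20% | 0.395 | 1.11 SD | 0.24 |

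**The case against.** The strongest reply is that the article gives only the skeleton of the MMRM. It nowhere says that the stratification factors are excluded, and a covariate list is commonly left to a full protocol or analysis plan, which is not shown here. That stands as a limit: the point is conditional on the model being run as stated. It does not remove the point, because the article does state the model's factors and its power model, and neither includes the strata.

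A reader might infer that the precision gained by stratifying is thrown away, or that the result is biased. The simulation does not support either reading. The balance stays in the estimate (actual SD 0.1448 without the factors, 0.1436 with them, at q = 20%), and the error is on the conservative side. Nor do the documents show a trial short of power for this reason. With d = 0.5, pairwise power is 0.885 without the factors, above the 0.80 target.

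On age, one can fairly say that the Discussion question describes the wider eligibility range of 15 to 25 years and does not promise an interaction test, since the aims and hypotheses do not mention age. That is a reasonable reading and is why this part is minor. It does not fully dispose of the matter, because the article says the trial addresses the question. An interaction test would not settle it either, given the power shown above.

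**Conclusion.** The point holds in a limited form. If the stated model is used, inference on the treatment comparisons is valid but conservative. With an assumed 10% to 30% of residual variance explained by the strata, type I error is about 0.036 to 0.024, and power at d = 0.5 is lower by about 2 points (0.886 against 0.9095) to 6 points (0.898 against 0.959). At 0% there is no loss. The figures come from a single-time-point ANCOVA with assumed block size and stratum prevalences. The true share is not in the article, so the size is uncertain and the direction is not. The stated 40 per group is unaffected.

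The age mismatch is real but secondary. It calls for rewording and one exploratory estimate. It does not show that a planned objective has been dropped, since age is in none of the aims or hypotheses.

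**What to change.** Before treatment allocation is unblinded for analysis:

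1. State that age group, sex and CESD-R group, as used at randomisation, enter the primary and secondary MMRMs together with their interactions with time. In the model for CESD-R itself, do not enter baseline CESD-R as a covariate if it is already a response level; age group and sex remain.
2. Reword the Discussion question to ask whether differences between the three interventions vary by age group. Report one arm-by-age-group estimate at 12 months with its confidence interval, labelled exploratory. Say that only interactions of about 0.9 SD or more are detectable, depending on the age split, and that a non-significant result is not evidence of equal effect.

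No new data are needed, because all three factors are already recorded for randomisation. The cost is three parameters per visit: 3 × 4 = 12 if the four follow-up visits are the responses, or 3 × 5 = 15 if baseline is one as well.
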